### Eligibility Criteria

3.1

Inclusion criteria
i.Adults aged ≥ 18 years, receiving care within the Brazilian Primary Health Care Network.ii.At least one documented consultation with a primary care physician (PCP) within the last 36 months.iii.Ability to provide informed consent personally or via a legally authorized representative.iv.Access to a telephone or digital platform for remote follow‐up.v.Diagnosis of type 2 diabetes mellitus with glycated hemoglobin (HbA1c) ≥ 7.0% measured in a certified laboratory within the previous 18 months.vi.Presence of at least one additional uncontrolled cardiovascular risk factor at baseline:
−Uncontrolled hypertension, and/or−Uncontrolled LDL‐C.

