### Primary Efficacy Endpoint

6.1

The key primary efficacy endpoint is a standard win ratio composed of time to occurrence of all‐cause death and the number of non‐fatal cardiovascular hospitalizations from randomization to Week 84. These events will be identified using multiple verified data sources, including EHRs, discharge summaries, and official death certificates, and will undergo centralized review by the data management team to ensure accuracy and completeness across sites. The objectivity of these outcomes, combined with centralized validation procedures, minimizes the potential for ascertainment bias.

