## Sample Size Calculation

7

Given that a comprehensive multifactorial intervention targeting intensive cardiovascular risk factor control has been associated with significant reductions in cardiovascular mortality (−57%), cardiovascular events (−59%), and hospitalizations due to heart failure (HF) in patients with diabetes [1], this study was designed using a standard win ratio test. The win ratio test incorporates both all‐cause mortality and all‐cause hospitalizations, using component‐wise hazard ratios (HRs) as effect size estimators.

For the sample size estimation, predefined hazard ratios (HR 0.90 for all‐cause death and HR 0.70 for all‐cause hospitalization) were used, targeting 90% statistical power with a two‐sided *α* = 0.05% and 5% expected attrition. Sensitivity analyses explored plausible variations in baseline event rates and component HRs to confirm robustness of the win‐ratio and power assumptions. A total of 838 participants (419 per treatment arm) will provide adequate power under these scenarios. Sample size calculations were performed in R (v1.2) using the WR package, as described by Mao et al. and Yu et al. [14, 15]. Supporting Information Material 4 summarizes the simulation scenarios and corresponding sample size estimates.

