### Statistical Methods

9.4

All continuous variables will be presented as median and interquartile range (IQR), while categorical variables will be reported as absolute (n) and relative frequency (%).

Descriptive statistics (mean ± standard deviation, median and IQRs) will be generated for each treatment group to summarize demographic and baseline characteristics. Between‐groups comparisons will be conducted within the Intention‐to‐Treat (ITT) population to ensure that the randomization process successfully achieved balance between groups. Differences in baseline characteristics between treatment groups will be tested using a chi‐square test for categorical variables and a two‐tailed *t*‐test with treatment as a factor for continuous variables. These preliminary analyses will serve as an initial assessment of the adequacy of randomization.

The primary endpoint analysis will be performed using a win‐ratio test, which combines time to all‐cause death and the frequency of nonfatal hospitalizations. The win ratio test will follow the original methodology described by Pocock et al. [16]. Beyond hierarchical endpoint evaluation, this approach allows for the integration of multiple endpoint types. Treatment differences will be tested at an alpha level of 0.05, with a sequential procedure for controlling type 1 error. Additional covariate adjustments for time‐sensitive analyses will be performed using a Cox proportional hazards model, incorporating the randomization stratification factor. The HR for treatment groups will be reported along with the 95% confidence interval (CI).

The secondary endpoint analysis will be performed using Kaplan‐Meier survival curves, evaluating time‐to‐event data for each secondary efficacy endpoint. The log‐rank test used for the primary endpoint analysis will also be applied to secondary endpoints. Treatment differences will be tested at an alpha level of 0.05, employing a sequential procedure for type 1 error correction. Covariate adjustments for time‐dependent analyses will again be performed using the Cox proportional hazards model, with the HR and 95% CI reported.

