For non–time‐to‐event secondary endpoints, including changes in metabolic and clinical parameters (blood pressure, HbA1c, LDL‐C) and patient‐reported outcomes, analyses will be performed using paired t‐tests and analysis of covariance (ANCOVA) models, incorporating baseline values as covariates. Treatment differences will be evaluated at a two‐sided alpha level of 0.05, applying the same hierarchical procedure used for time‐to‐event endpoints to control type I error. All analyses will follow the ITT principle, and sensitivity analyses will be conducted to assess the impact of missing data.

For the tertiary endpoint analysis, the study will evaluate changes in the MeTaRiSc from baseline to Week 84. Each participant will receive a score of 1 for each parameter above the target; the total score will then be divided by three, producing a weighted mean ranging from 0 to 1. A paired t‐test will compare the two treatment groups. Treatment differences will be tested at an alpha level of 0.025, using a sequential type 1 error correction procedure. Covariate adjustments will be made using a *t*‐test, incorporating the randomization stratification factor. The mean values for each treatment group (intervention vs. control) will be reported with the corresponding 95% CI.

All subgroup analyses will involve log‐rank tests and the hazard ratios (with 95% CIs) for primary and secondary efficacy endpoints. The predefined subgroups include sex, age (< 65 vs. ≥ 65 years), prior cardiovascular disease, presence of cardiovascular risk factors (diabetes, hypertension, chronic kidney disease), smoking history (active vs. significant past smoking), obesity/metabolic syndrome, and prior statin use.

The present study was designed in accordance with the NIH‐FDA Clinical Trial Protocol Template. A structured protocol and a Statistical Analysis Plan (SAP) were developed prior to participant enrollment, specifying the analytic approach for all predefined endpoints, including sensitivity and subgroup analyses.

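### A stray clause calls the primary test a log-rank test, subgroups of the win-ratio endpoint are set on a hazard-ratio scale, and the diabetes subgroup is empty

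*Protocol article*

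**What the plan says.** All references are to the protocol article.

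- **Primary test.** Section 9.4 states: "The primary endpoint analysis will be performed using a win‐ratio test". This matches the abstract, the endpoint definition in section 6.1 ("The key primary efficacy endpoint is a standard win ratio composed of time to occurrence of all‐cause death", with a count of non-fatal hospitalizations as the second component) and section 7 ("this study was designed using a standard win ratio test").
- **Next paragraph of section 9.4, on secondary endpoints.** It says: "The log‐rank test used for the primary endpoint analysis will also be applied to secondary endpoints".
- **Subgroups, later in section 9.4.** "All subgroup analyses will involve log‐rank tests and the hazard ratios (with 95% CIs) for primary and secondary efficacy endpoints". The listed factors include "presence of cardiovascular risk factors (diabetes, hypertension, chronic kidney disease").
- **Eligibility, section 3.1.** Every participant must meet this criterion: "Diagnosis of type 2 diabetes mellitus with glycated hemoglobin" at or above 7.0%.
- **Strata.** Section 9.2 stratifies randomization by age, gender and prior cardiovascular disease. Section 9.4 mentions the stratification factor for the primary endpoint only in connection with an additional Cox model.

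**The concern.** A confirmatory trial needs one named primary test. Here consecutive paragraphs attach two different names to it. The log-rank test compares times to one event per person, whereas the stated endpoint ranks pairs first on death time and then on number of hospitalizations. The two do not estimate the same quantity.

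The subgroup paragraph turns this from a slip into an instruction. A programmer who followed it would need a time-to-event variable for the primary endpoint, and the document defines none. The likely choice, time to first death or hospitalization, drops the priority of death and ignores repeat admissions. The subgroup display would then describe a different estimand from the headline result, and agreement or disagreement between subgroups would say little about the win ratio.

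The diabetes item is simpler: it asks for a contrast that the eligibility criteria rule out.

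**Working it through.** **1. Which primary test does the document specify?**

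| Place | Test attached to the primary endpoint |
|---|---|
| Abstract | win ratio |
| Section 6.1 | win ratio |
| Section 7 | win ratio |
| Section 9.4, primary paragraph | win ratio; Cox as an additional adjusted analysis |
| Section 9.4, secondary paragraph | log-rank, referred to as if already specified |
| Section 9.4, subgroup paragraph | log-rank and hazard ratios |

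The first four agree. The fifth points back to something that does not exist in the text. The Cox model does not explain it, because that is a covariate-adjusted addition and not a log-rank test. The sixth is a live instruction.

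**2. Is a hazard ratio defined for the primary endpoint?** The endpoint compares each intervention patient with each control patient: death time first, then hospitalization count if the first step is tied. The result is wins divided by losses. Each component can have its own hazard or rate ratio, and section 7 uses 0.90 for death and 0.70 for hospitalization as planning values. The hierarchy as a whole has no single hazard ratio. The subgroup paragraph does not say which event is meant.

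**3. Does the choice of test affect power?** The plan's 838 cannot be reproduced in full, because the baseline event rates are in Supporting Information Material 4, which is not shown. The attrition step fits: 398 / (1 − 0.05) = 418.9, rounded up to 419 per arm, and 2 × 419 = 838. A simulation used 398 evaluable per arm, 84 weeks, the two planning ratios, two-sided alpha 0.05, 300 runs per scenario and assumed control rates. At 0.4 hospitalizations per year:

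| Assumed death rate per year | Win ratio (death, then count) | Log-rank, first event |
|---|---|---|
| 0.02 | 0.913 | 0.863 |
| 0.05 | 0.883 | 0.887 |

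With 300 runs, the Monte Carlo standard error near 0.90 is √(0.9 × 0.1 / 300) = 0.017. Power is broadly similar, so the problem is the estimand and not lost power.

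**4. What if both tests were run and the better one reported?** For two null z-statistics with correlation r, the error rate is P(|z₁| > 1.96 or |z₂| > 1.96) under a bivariate normal:

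| r (assumed) | Type I error |
|---|---|
| 0.80 | 7.8% |
| 0.90 | 7.0% |
| 0.95 | 6.5% |

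The document gives neither r nor any sign of such a choice. In the simulation above, counts and first-event times were drawn independently, so it cannot supply r.

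**5. The diabetes subgroup.** Eligibility requires type 2 diabetes, so 838 of 838 have it and 838 − 838 = 0 do not. If the listed risk factors are read as one combined item, everyone is still positive and the contrast stays empty. Hypertension and chronic kidney disease, read separately, can still form contrasts.

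**6. Would stratifying the win ratio help?** A simulation of 350 runs over 8 strata compared unstratified with stratified power. With prior cardiovascular disease at hazard ratio 3 and age at 1.5, power went from 0.849 to 0.863, a difference of 0.014 × 350 ≈ 5 runs. With cardiovascular disease at hazard ratio 2, it went from 0.891 to 0.894, about 1 run. The standard error of one such estimate is √(0.85 × 0.15 / 350) = 0.019, so neither gain stands out from simulation noise.

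**The case against.** The strongest reply is that nobody could be misled about the primary test. It is a win ratio wherever it is defined, sized or described. The log-rank words are a passing clause in the paragraph on secondary endpoints and name no event, so they could not be carried out as a rival analysis. Section 9.4 also says that an analysis plan was written before enrollment. This largely stands. A reader might infer two competing primary p-values and an inflated error rate. The document does not support that: it specifies only one usable primary analysis, and the error rates above need both an assumed correlation and an assumed choice made after seeing the data. The clause is still wrong as printed, and an analysis plan that is not shown does not correct it.

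A second reply is that the subgroup hazard ratios may be meant component by component, as in the sample size section. That is plausible, but the text says primary endpoint and names no component. Even on that reading, the results would be on another scale from the win ratio.

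Third, an unstratified win ratio is a valid test. Agreed: leaving the strata out is not an error.

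Fourth, the empty diabetes subgroup harms neither the primary result nor its error rate. That is also true, and it is why it is a small correction.

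**Conclusion.** The point holds in a limited form and should be fixed; it does not threaten the design. Three things are wrong as written: a clause that names a primary log-rank test specified nowhere, a subgroup method that does not fit the hierarchical endpoint, and a diabetes subgroup with 0 of 838 participants on one side. The first and third rest on the text alone. The second rests on the endpoint definition in section 6.1.

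The consequence is unclear subgroup reporting: those results could not show whether the win ratio is consistent across patients. Loss of power is not the issue under the assumed rates. The range of 6.5% to 7.8% is an illustration of why a single test must be named, not an estimate of this trial's error rate. Stratification is an optional improvement whose gain could not be distinguished from noise.

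**What to change.** In section 9.4, and in the analysis plan where it carries the same wording:

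1. Delete the clause that calls log-rank the primary test, and state that the win ratio is the sole primary test. Name the log-rank test directly for those secondary endpoints that are times to an event.
2. Label Cox and log-rank analyses of death and of first hospitalization as supportive.
3. For subgroups of the primary endpoint, report a win ratio in each level with an interaction test, for example the difference in log win ratios divided by the root of the summed squared standard errors.
4. Remove diabetes from the subgroup list.
5. Optionally, stratify the win ratio by the randomization factors (age, gender, prior cardiovascular disease). If adopted, fix this before any outcome comparison by arm.

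The cost is wording and programming. Sample size, visits and data collection do not change.

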**Methods:**

This is an open‐label randomized and decentralized clinical trial describing the design and methodology of the TAMIS program, which will assess its impact on community‐dwelling diabetic subjects with uncontrolled HBA1c and uncontrolled LDL‐C and/or blood pressure. Individuals will be randomized to usual care or remote care and followed for 84 weeks. Remote monitoring offers a practical response to the limited capacity of LMIC health systems to ensure sustained follow‐up and continuity of care for chronic conditions. The primary endpoint is a win‐ratio of hierarchical events, including all‐cause deaths and the frequency of all‐cause hospitalizations. The secondary endpoints include control of HbA1c, LDL‐C and blood pressure according to clinical guidelines, as well as patient‐reported outcomes and clinical parameters, including blood pressure, glycemic control, and LDL cholesterol levels. Subgroup analyses will explore the impact of demographics and clinical characteristics on treatment outcomes. Overall, the study aims to improve health care delivery, enhance patient education, and foster collaboration between patients and health care providers to mitigate the growing burden of cardiovascular diseases in LMICs.

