**Figure 1 jep70456-fig-0001:**
[figure not shown]
Overview of patient flow and study design.

Participant selection and randomization involve confirming interest, explaining the study details, and assessing eligibility. Baseline demographic data, medical history, and health status will be collected before randomization. During follow‐up visits, the study team will: (i) measure blood pressure and glycemic levels; (ii) administer the study protocol; (iii) monitor symptoms and adverse events, and (iv) evaluate treatment adherence.

Adherence will be defined as the completion of at least 80% of scheduled home measurements and the use of at least 80% of prescribed medication doses during follow‐up. Data will be obtained through the TAMIS‐IA platform and scheduled study visits. Participants meeting both criteria will be classified as adherent in secondary analyses. Low adherence will be addressed through sensitivity analyses.

At baseline and weeks 12, 24, 36, 56, and 84, blood samples will be collected, laboratory tests performed, and study endpoints assessed. At week 84, similar follow‐up procedures will take place, with additional endpoint evaluations and final blood sample collection. In addition to these scheduled in‐person laboratory assessments, follow‐up incorporates structured remote contacts and digital data capture. Participants are not required to attend in‐person visits for each follow‐up interaction. In the intervention arm, counseling and medication titration discussions are conducted remotely by trained monitors under physician supervision. Throughout the study, all data will be systematically documented and entered into a secure database. Additionally, quality of life will be assessed using the European Quality of Life 5 Dimensions (EQ‐5D) and the ICEpop Capability Measure for Adults (ICECAP‐A) at multiple time points. The description of the study procedures and measurements is provided in Supporting Information Material 1: Schedule of Activities and illustrated in Figure 2.

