### Secondary Efficacy Endpoints

6.2

The key secondary efficacy endpoints are time from randomization to the first occurrence of the composite of the following events:
84‐week change in Quality‐of‐life assessment by the EQ‐5D and ICECAP‐A.12‐, 56‐ and 84‐week adherence to home BP measurements.12‐, 56‐ and 84‐week prescription and adherence to anti‐hypertensives, lipid‐lowering, and anti‐hyperglycemic therapies.

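### Section 9.4 names only paired t-tests and baseline-adjusted ANCOVA for secondary endpoints that are not time-to-event; these do not suit the yes/no endpoints and cannot be run as written on home-BP adherence

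*Protocol article*

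**What the plan says.** Section 9.4 (Statistical Methods) gives one rule for secondary endpoints that are not time-to-event: paired t-tests and "analysis of covariance (ANCOVA) models, incorporating baseline values as covariates". Blood pressure, HbA1c, LDL-C and patient-reported outcomes are introduced by the word including, so they are examples and not the full scope. The same paragraph sets a two-sided alpha of 0.05 and places these endpoints in the type I error hierarchy ("applying the same hierarchical procedure used for time"-to-event endpoints).

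Section 6.2 lists change in EQ-5D and ICECAP-A at week 84. It also lists, for weeks 12, 56 and 84, "week adherence to home BP measurements" and both prescription of and adherence to three drug classes.

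Section 2.1 defines adherence by two 80% thresholds, one for scheduled home measurements and one for prescribed doses, both accrued over follow-up. It adds: "Participants meeting both criteria will be classified as adherent in secondary analyses". The abstract names a further set: "The secondary endpoints include control of HbA1c", LDL-C and blood pressure to guideline targets.

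Two other statements claim the same endpoints. The opening line of section 6.2 introduces its list as a time-to-first-event composite. An earlier paragraph of section 9.4 applies Kaplan-Meier curves and the log-rank test to every secondary efficacy endpoint.

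**The concern.** The rule is written for a continuous outcome measured before and after randomization. Several secondary endpoints are neither continuous nor measured before randomization. The article names no test of proportions for any outcome; its chi-square test is only for baseline characteristics.

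This matters because the endpoints sit in a testing hierarchy, where every step needs a defined test and effect measure. It matters more in an open-label trial, where section 8 says patients, investigators, monitors and clinical staff know the allocation. A reader of the article cannot tell whether adherence will be reported as a mean difference, a risk difference or a hazard ratio.

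**Working it through.** The plan gives no figure on this point to reproduce. The check sets endpoint type against stated method.

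**1. Endpoint by endpoint**

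| Endpoint | Type | Baseline value | Stated method |
|---|---|---|---|
| Change in EQ-5D, ICECAP-A (6.2) | score | implied by change | ANCOVA fits |
| Change in BP, HbA1c, LDL-C (9.4) | measurement | yes | ANCOVA fits |
| Home-BP adherence (6.2) | yes/no at 80% (2.1) | none described; home measurement starts on enrollment (5.2) | cannot be run as written |
| Drug adherence, three classes (6.2) | yes/no at 80% of doses (2.1) | none, unless also measured at baseline, which is neither stated nor excluded | cannot be run as written unless a baseline is taken |
| Prescription, three classes (6.2) | yes/no on natural reading | obtainable from the baseline history | runs, unsuited |
| Control of HbA1c, LDL-C, BP (abstract) | yes/no | baseline measurement | runs, unsuited |

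**2. The paired t-test.** It tests the mean within-person difference between two occasions. It gives no contrast between arms for any endpoint in the table, and with no baseline there is no pair.

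**3. How many section 6.2 endpoints are yes/no**
- By drug class and week: 2 quality-of-life + 3 home-BP adherence + 3 × 3 prescription + 3 × 3 drug adherence = 23. Yes/no: 3 + 9 + 9 = 21, and 21/23 = 91%.
- By class only: 2 + 1 + 3 + 3 = 9. Yes/no: 1 + 3 + 3 = 7, and 7/9 = 78%.
- By kind (EQ-5D, ICECAP-A, home-BP adherence, prescription, drug adherence): 3/5 = 60%.

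Yes/no endpoints are the majority on every count.

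**4. How many lack a baseline.** By class and week, 3 + 9 = 12 of 23 (52%); by class, 1 + 3 = 4 of 9 (44%); by kind, 2 of 5 (40%). If drug adherence is also measured at baseline, only 3 of 23 (13%) lack one. Taking the three bullets of section 6.2 as units, with prescription pooled with adherence, gives 2 of 3 (67%). The share is set by the counting rule.

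**5. Can a linear model run on a yes/no endpoint?** Simulation with no treatment effect, 398 per arm (419 × 0.95 = 398.05), two-sided 0.05, 4,000 runs per setting. The yes rates and the two-level baseline covariate are assumptions.

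| Yes rate | No covariate | With baseline covariate |
|---|---|---|
| 0.5 | 0.052 | 0.053 |
| 0.8 | 0.053 | 0.050 |
| 0.9 | 0.048 | 0.054 |

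The Monte Carlo standard error is √(0.05 × 0.95 / 4000) = 0.0034, so all six values agree with 0.05. The model runs and holds its level.

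**6. If a baseline covariate were the same for everyone.** The design matrix (intercept, arm, baseline) has rank 2 of 3. The baseline term drops out and an unadjusted two-group comparison remains.

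**The case against.** The strongest reply is that a journal article condenses, and section 9.4 says an SAP written before enrollment covers the analysis of all predefined endpoints. That stands against any claim of omission: a reader might infer that the test would be picked after the data are seen, and the article does not support this. It does not rescue the sentence itself, which states a method for the whole class. If the SAP has a binary method, the article departs from it; if it repeats the sentence, the defect is there too.

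A second reply is that the yes/no reading is partly interpretation. The explicit classification in section 2.1 is joint (both criteria met), whereas section 6.2 lists home-BP and drug adherence separately, and either could be analysed as a percentage. That is possible, but the 80% cut-offs point to yes/no, and a percentage of home measurements completed would still have no baseline.

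A third is that the time-to-event statements in sections 6.2 and 9.4 may govern these endpoints. That adds a contradiction and does not supply a method, since adherence and prescription are assessed at fixed weeks.

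Two stronger readings should be resisted:
- A reader might infer that no yes/no endpoint can be analysed as stated. Step 5 shows otherwise.
- A reader might infer that baseline HbA1c control is constant because entry requires HbA1c of at least 7.0%. The qualifying value may be up to 18 months old and blood is drawn at baseline, so status can vary. The article also speaks of baseline values, most naturally the measurement, and never proposes a control flag. No loss of precision can be charged to it.

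**Conclusion.** The point holds as a mismatch between stated method and endpoint type. The paired t-test does not compare arms for any endpoint. For home-BP adherence at its three time points the stated analysis has no executable form; the same applies to drug adherence on the assumption that it is not also measured before randomization. For prescription and guideline control the method is unsuited: it runs at about the right type I error (0.048 to 0.054), but a model and effect measure for proportions is the usual choice.

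Yes/no endpoints make up 60% to 91% of the section 6.2 list, taking prescription as yes/no and adherence as defined in section 2.1. A reader might infer that most endpoints lack a baseline; the counts tried range from 13% to 67%, so no such headline is supported. The primary endpoint and the continuous secondary endpoints analysed by ANCOVA are unaffected. The correction is worth making before analysis, but the point does not threaten the trial's main result.

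**What to change.** In section 9.4, and in the SAP if it repeats the sentence:
- Drop the paired t-test as a comparison between arms.
- Limit ANCOVA to continuous endpoints with a baseline: BP, HbA1c, LDL-C, EQ-5D and ICECAP-A.
- State that yes/no endpoints (adherence, prescription, control of HbA1c, LDL-C and BP) are compared between arms with a binary-outcome model. Logistic regression reported as a standardized risk difference with 95% CI is one good choice; others are acceptable if named.
- Adjust for the randomization strata in section 9.2: age group, gender and prior cardiovascular disease.
- Add a baseline term only where one exists: the continuous baseline measurement for control endpoints, baseline prescription of the class for prescription endpoints, none for home-BP adherence, and none for drug adherence unless it is measured before randomization.
- In the same edit, remove or reconcile the time-to-first-event lead-in of section 6.2 and the section 9.4 instruction to apply Kaplan-Meier and log-rank to each secondary endpoint. Correcting only the ANCOVA sentence would leave a competing method in place.

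The cost is a few lines of text and one more model type to program. No new data, visits or participants are needed.

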### Tertiary Efficacy Endpoint

6.3

The change in the ‘metabolic target risk score’ (MeTaRiSc) from baseline to week 84. Each individual will be assigned the value 1 for each parameter above the targets, and the sum of the 3 parameters will be divided by 3. The MeTaRiSc is this weighted mean that varies from 0 to 1.
i.+1 if more than 10% of home SBP measurements ≥ 130 mmHg.ii.+1 point if LDL cholesterol levels are above targets defined by the 2013 ACC/AHA cholesterol guidelines;iii.+1 point if glycated hemoglobin (HbA1c) levels ≥ 7.0%.

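### The tertiary endpoint (MeTaRiSc) is to be compared between two independent arms with a paired t-test and adjusted with a t-test; neither can do that job

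*Protocol article*

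**What the plan says.** Section 6.3 (Tertiary Efficacy Endpoint) defines the endpoint as "The change in the ‘metabolic target risk score’ (MeTaRiSc) from baseline to week 84". The score counts how many of three parameters (home systolic pressure, LDL-C, HbA1c) are above target and divides by three, so it runs from 0 to 1.

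Section 9.4 (Statistical Methods) gives the analysis of this endpoint in four statements:

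- Test: "A paired t‐test will compare the two treatment groups".
- Level: "Treatment differences will be tested at an alpha level of 0.025, using a sequential type 1 error correction procedure". It does not say whether this is one- or two-sided.
- Adjustment: "Covariate adjustments will be made using a *t*‐test, incorporating the randomization stratification factor".
- Reporting: the mean of each arm with a 95% CI. No between-arm difference is named.

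For the non-time-to-event secondary endpoints the same section says "analyses will be performed using paired t‐tests and analysis of covariance (ANCOVA) models, incorporating baseline values as covariates", followed by "Treatment differences will be evaluated at a two‐sided alpha level of 0.05".

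The Abstract says that individuals are randomized to usual care or remote care. Section 9.2 (Type of Randomization) describes permuted blocks of four to eight within strata formed by age (below 55, or 55 and over), gender and prior cardiovascular disease.

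**The concern.** A paired t-test analyses differences within natural pairs. Individual randomization in blocks creates two independent groups and no pairs between them. The only natural pairs in this trial are a participant's own baseline and week-84 values, and a test on those asks whether an arm changed, not whether the arms differ. The adjustment sentence does not rescue the analysis, because a t-test has no term for strata.

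This is a method stated wrongly. It is not a detail left to an analysis plan that is not shown.

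MeTaRiSc is the only endpoint listed under Outcomes (Section 6) that measures joint control of pressure, LDL-C and HbA1c, which is what the program is meant to change. Eligibility requires HbA1c of at least 7.0% plus uncontrolled hypertension and/or LDL-C, so participants are selected with high scores. A fall in both arms is therefore expected without any treatment effect, and usual-care physicians also adjust treatment. If the analysis were carried out within arms, a fall that usual care also produced could be taken for an effect of the program.

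**Working it through.** **No figure to reproduce.** The article gives no effect size or power for MeTaRiSc. The 838 participants (419 per arm) belong to the win-ratio primary endpoint.

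**Step 1: the design against the test.** Allocation is individual, in parallel arms, with permuted blocks inside 2 × 2 × 2 = 8 strata. Block mates share a stratum and a time of entry, but a block of four to eight contains several participants per arm and defines no one-to-one match. The paired test can therefore be carried out in only two ways: (a) baseline against week 84 inside each arm, or (b) changes in one arm paired arbitrarily with changes in the other.

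**Step 2: illustrative simulation.** Inputs:

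- Evaluable participants per arm: 419 × 0.95 = 398 (the article's 5% attrition).
- Level: 0.025, taken as two-sided (assumption).
- Baseline probabilities of being above target on the three parameters: 0.8, 0.8 and 1.0 (assumption).
- Parameters independent of each other and over time (assumption).
- 5,000 replicates per scenario.

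The mean fall in the score is the sum of the three drops in probability divided by 3. In every scenario below both arms have the same distribution, so the true treatment effect is zero.

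| Week-84 probabilities, both arms | Mean fall | (a) intervention arm significant | (a) exactly one arm significant | (b) arbitrary pairs significant | Two-sample test on changes significant |
|---|---|---|---|---|---|
| 0.784, 0.784, 0.98 | (0.016 + 0.016 + 0.02)/3 = 0.017 | 16.2% | 27.6% | 2.3% | 2.3% |
| 0.78, 0.78, 0.97 | (0.02 + 0.02 + 0.03)/3 = 0.023 | 28.4% | 41.3% | 2.5% | 2.5% |
| 0.72, 0.74, 0.90 | (0.08 + 0.06 + 0.10)/3 = 0.080 | 99.9% | 0.2% | 2.6% | 2.6% |

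The discordance column follows 2p(1 − p) for independent arms. With p = 0.284 this gives 2 × 0.284 × 0.716 = 0.41.

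**Step 3: execution (a).** The rejection rate tracks the common fall and carries no information about treatment. With a small common fall the arms often give opposite verdicts. With a larger one, both arms are almost always significant.

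**Step 4: execution (b).** Type I error is close to 2.5%, so this version is not invalid in that sense. Its p-value is arbitrary, however. In one simulated dataset with a true difference between arms, the two-sample p was 0.052, while the paired p ranged from 0.033 to 0.072 over 2,000 row orderings. That range straddles 0.05, though not 0.025. The version also needs equal evaluable numbers in the two arms, which attrition will not guarantee.

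**Step 5: a correct comparison.** The two-sample test on changes held its level (2.3% to 2.6%). An ANCOVA also compares the independent arms and can carry the strata. It was not simulated.

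**The case against.** The best defence is that this is loose wording for a two-sample t-test on changes from baseline. The tertiary text speaks of treatment differences and of two group means, it specifies no within-arm analysis, and elsewhere in Section 9.4 an ordinary two-tailed t-test with treatment as a factor is used for baseline comparisons. This is plausible, and it means that one cannot predict that a within-arm result would be reported as a treatment effect. It does not remove the fault. The section evidently distinguishes the two tests and names the paired one here, and the adjustment sentence fails on any reading.

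Three stronger readings are tempting, and the article does not support them:

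- **That the continuous secondary endpoints also lack a valid between-arm comparison.** They do not. The sentence that names paired t-tests also names ANCOVA with baseline as covariate, which is a valid comparison. What remains is that the text does not say which method is inferential.
- **That the 0.025 level is an error because other tests use 0.05.** A stricter level at the lowest tier does not inflate type I error, and moving it to 0.05 would be a preference. Only the missing sidedness needs attention.
- **That the tertiary result could not be computed at all.** Arbitrary pairing is computable and roughly holds its level. Its defects are order dependence and the need for equal numbers.

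**Conclusion.** The tertiary analysis is wrong as written: the named test has no pairs to work on, the named adjustment cannot adjust, and no alternative is given. Severity is moderate. One tertiary endpoint is affected; the primary win-ratio analysis and the sample size do not depend on it.

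That the test does not fit the design follows from the text alone. The percentages do not: they rest on assumed score distributions and show a range, not a forecast. The size of the expected common fall is also uncertain. Qualifying values may be up to 18 months old, so if the baseline score uses fresh measurements, part of the regression to the mean will already have happened before baseline.

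**What to change.** Replace the tertiary test and adjustment sentences with: Week-84 MeTaRiSc will be compared between arms by ANCOVA with treatment, baseline MeTaRiSc and the stratification factors (age group, gender, prior cardiovascular disease) as terms; the adjusted mean difference between arms will be reported with its 95% CI.

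State whether the 0.025 level is one- or two-sided.

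For the continuous secondary endpoints, state that ANCOVA is the between-arm test and that paired t-tests serve only to describe change within an arm.

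The cost is a wording change in the protocol and the analysis plan. Baseline values and strata are already collected, and neither the sample size nor the primary analysis changes. The change should be made before the data are analysed.
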